## Abstract

**Introduction:**

Post-stroke depression (PSD) is an emotional disease characterized by loss of interest and depression after a stroke. Acupuncture, one of the most critical non-drug therapies for the treatment of PSD, has significant clinical efficacy, but the mechanism is not fully understood. Previous study has shown that acupuncture can reduce the level of proinflammatory cytokines and increase the level of anti-inflammatory cytokines, suggesting that regulating the dynamic balance of inflammatory cytokines may be the basis for acupuncture to improve PSD symptoms.

**Methods and analysis:**

A total of 84 patients with PSD will be recruited and randomly assigned to one of two groups at a 1:1 ratio. Based on the conventional stroke treatment, the control group will receive XingnaoKaiqiao (XNKQ) acupuncture, and the experimental group will receive antidepressant acupuncture at the same time as XNKQ acupuncture. The intervention will last four weeks, and data will be collected before and after treatment. The Hamilton depression scale (HAMD-17) is the primary outcome measure, and the secondary outcome measures include the Self-rating Depression Scale (SDS), the National Institute of Health stroke scale (NIHSS), and the Modified Barthel Index (MBI). Serum IL-1β, IL-4, 5-HT, and BDNF will be used as laboratory indicators. The scales will be assessed at baseline, two weeks, and four weeks, and serum items will be measured at baseline and four weeks after treatment. This study will observe the clinical effect of acupuncture on PSD and the changes in serum-related inflammatory cytokines and explore the possible mechanism of acupuncture against depression from the perspective of inflammatory response.

**Ethics and dissemination:**

This study protocol was approved by the Medical Ethics Committee of the First Teaching Hospital of Tianjin University of Traditional Chinese Medicine (item number: TYLL2023[Z]004). Findings of the trial will be disseminated through peer-reviewed journals and scientific conferences.

## 1 Introduction

Post-stroke depression (PSD) is an affective disorder complication characterized by depression and loss of interest after a stroke, which has recently attracted more attention. According to statistics, the incidence rate of PSD in the first year of stroke is about 10% to 15%, and the incidence rate in 5 years is 39% to 52% [1]. In China, the incidence of PSD is around 34.9%, with women being more affected than men [2]. A recent animal experiment has emphasized the importance of sex specificity in determining PSD [3].

PSD manifests mainly as emotional apathy, weight change, sleep disturbance, fatigue, a sense of worthlessness, and anhedonia [4]. PSD is a negative prognosis in stroke recovery, frequently resulting in higher mortality, poorer functional recovery, significant cognitive impairment, and decreased quality of life [5].

It is essential to clarify the etiology and pathogenesis of PSD for its treatment. The occurrence of PSD is the result of a combination of social psychological factors and biological factors, including axis dysregulation, increased inflammatory factors, decreased monoamine levels, glutamate-mediated excitotoxicity, and abnormal neurotrophic responses [6, 7]. Among them, the theory of inflammatory response is one of the hotspots in the current research on the mechanism of PSD. Various inflammatory factors, primarily pro-inflammatory and anti-inflammatory cytokines that oppose each other, are implicated in the incidence of PSD, with different expressions in different phases of PSD. As antidepressant drugs can cause changes in inflammatory factors, changing the balance of inflammatory factors may be one of the strategies for treating PSD [8].

Currently, the first-line treatment for PSD is selective serotonin reuptake inhibitors (SSRIs), which can prevent and treat depression in PSD patients. However, adverse reactions such as cerebral hemorrhage, epilepsy, and gastrointestinal symptoms have increased to some extent [9]. Given the limitations of pharmacological treatment, several non-drug treatments, such as non-invasive brain stimulation, psychotherapy, exercise therapy, acupuncture, music, literature, and art, have been employed in the clinical treatment of PSD [10].

Acupuncture is an essential element of TCM (Traditional Chinese Medicine), and its therapeutic efficacy in the treatment of PSD is well-known. Acupuncture has been shown in several clinical studies to significantly improve the depressive symptoms of PSD patients, enhancing their quality of life [11–15]. Several systematic reviews have shown that acupuncture significantly improves HAMD and NIHSS scores [16, 17]. Another study found that electroacupuncture improves symptoms of PSD patients as does antidepressant drugs, with a higher safety [18]. Studies have found that acupuncture treatment of PSD may be an overall regulation of multiple aspects and targets. The specific mechanism basically involves neurotransmitter regulation, neuroendocrine disorders improvement, inflammatory factor reduction, oxidative stress reduction, neuron protection, and regeneration promotion [19]. Our previous studies have shown that acupuncture can reduce the levels of pro-inflammatory factors and increase the anti-inflammatory factors to regulate the dynamic balance of inflammatory factors, which may be one of the mechanisms for acupuncture to improve PSD [20]. According to the preliminary clinical observation, acupuncture can improve the depressive symptoms of PSD patients, the motor function of limbs, and the quality of life [15].

At the moment, the mechanism of acupuncture treatment for PSD remains unknown. Although the research evidence from animals and humans has gradually increased in recent years, more is required to be firmly proven [21]. Most clinical trials are small in scale, so there is insufficient evidence for the true efficacy of PSD patients. Therefore, while evaluating the clinical effectiveness of acupuncture for PSD through this project, it is of great significance to observe the effect of acupuncture on the inflammatory factors of PSD patients, further explore the mechanism of acupuncture for PSD, and provide a theoretical basis for clinical acupuncture treatment of PSD.

## 2 Method and analysis

### 2.1 Study design

A single-center, prospective, parallel-group, randomized controlled trial will be conducted in the First Teaching Hospital of Tianjin University of Traditional Chinese Medicine. A total of 84 PSD patients will be recruited, with those who satisfy the inclusion criteria being randomly assigned to one of two groups. One group will receive XNKQ acupuncture mainly, and escitalopram will be taken orally, and the other group will receive antidepressant acupuncture in addition to the above acupuncture treatment. All acupuncture treatments will be given six times a week for four weeks (orally take escitalopram tablets daily for 4 weeks). Outcomes include scale indicators, serum laboratory indicators, and metabolomics analysis results. The primary outcome is depressive symptom severity and corresponding changes, as assessed by the Hamilton Anxiety Scale (HAMD-17). The secondary outcomes are the severity of neurological deficit symptoms, quality of life, laboratory indicators, and serum metabolomics analysis in PSD patients. These results will be assessed by the National Institutes of Health Stroke Scale (NIHSS) and Modified Barthel Index Scale (MBI), self-rating depression scale (SDS) for self-assessment, and laboratory indicators including the determination of serum IL-1β, IL- 10 5-HT, and BDNF levels. Evaluators will conduct assessments at baseline, week 2, and week 4 (serum indicators and metabolomics analysis will be assessed at baseline and week 4). The flow chart of this trial is displayed in **Fig 1**, and the enrollment schedule is illustrated in **Table 1**.

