#### 2.5.1 Control group

Patients in the control group will receive conventional rehabilitation treatment with medication and acupuncture for 4 weeks.

Acupuncture treatment based on XNKQ Acupuncture for stroke dysfunction, acupoint locations are as described in **Table 2**. Acupoints include Shuigou (DU26), bilateral Neiguan (PC6), affected side Sanyinjiao (SP6), affected side Jiquan (HT1), affected side Chize (Lu5), affected side Weizhong (BL40), affected side Hegu (LI4), affected side Zusanli (ST36). The patient is placed in a supine position. After skin disinfection, the acupuncturist holds a disposable acupuncture needle (0.25mm×40mm Hwato brand, Suzhou Medical Supplies Factory Co., Ltd., Suzhou, China) for acupuncture operation. It should be noted that XNKQ Acupuncture uses a specific operation method, which is explained in Table 2. The acupuncture method is used to “De Qi” before the acupuncture is performed. Then all needles would be removed after being retained for 30 minutes. All patients will receive treatment six times each week for four weeks.Oral escitalopram tablets 10mg Qd for 4 weeks.

**Table 2 pone.0303162.t002:** Specific acupuncture methods and locations of acupoints.

Acupoints	Location	Insert angle	Insert depth
Baihui* (DU20)	On the head, 5 cun directly above the midpoint of the anterior hairline	15°	3 to 5 mm
Yintang* (EX-HN3)	On the head, at the intersection of the line between the two brows and the front midline	45°	10 to 15 mm
Fengfu* (DU16)	On the neck, 1 cun straight above the middle of the posterior hairline, the external occipital protuberance goes straight down, and the depression between the trapezius muscles on both sides	45°	15 to 20 mm
Shen* (CO10)	Located in the auriculae boat, on the ear wheel, below the foot fork, on the ear wheel foot below the rear, the 10^th^ area of the concha	90°	2 to 3 mm
Xin* (CO15)	Located in the depression in the middle of the concha cavity, that is, the 15th area of the concha	90°	2 to 3 mm
Shuigou**(DU26)	On the face, at the intersection of the upper 1/3 and middle 1/3 of the human midsulcus. In the orbicularis muscle (Sparrow-pecking acupuncture techniques until the eyeballs are wet with tears)	45°	5 to 10 mm
Neiguan** (PC6)	On the palm side of the forearm, between the palmaris longus tendon and the flexor carpi radialis tendon	90°	10 to 15 mm

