#### 2.5.2 Antidepressant acupuncture group

The patients will be placed in a semi-supine position, i.e., the bed rocker is elevated to 45°, and after skin disinfection, the treatment proceeds as follows.

The exact XNKQ acupuncture as in the control group is given, and the same acupuncture method is used to “De Qi” before the antidepressant acupuncture is performed [23]. Lifting-thrusting and twirling-rotating manipulations are acupuncture procedures used to make patients feel "De Qi," such as soreness, numbness, and swelling.Antidepressant acupuncture is given. The acupoint selections and ear-treating areas are Baihui (DU20), Yintang (EX-HN3), Fengfu (DU16), and auricular concha (corresponding to the auricular point Xin (CO15) and auricular point Shen (CO10)). The specific acupoint locations and operation diagram are shown in **Table 2** and Fig 2. The specific operations are as follows. The Baihui (DU20) point is inserted to a depth of 3 to 5 mm at an angle of 15°. The Yintang (EX-HN3) point is inserted to a depth of 10 to 15 mm at an angle of 45° (Needle tip towards the root of the nose). The Fengfu (DU16) point is inserted to a depth of 15 to 20 mm at an angle of 45° (Needle tip towards the Laryngeal node area). The auricular concha is equivalent to the position of the auricular point Xin (CO15) and auricular point Shen (CO10) of the auricular acupoint, with a depth of 2 to 3 mm and an angle of 90°. The two electrode clamps of the electroacupuncture instrument are then clamped to the shanks of the two acupuncture needles. Baihui (DU20) and Yintang (EX-HN3), connected to a group of electro-acupuncture, auricular acupoint Xin (CO15) and acupoint Shen (CO10) connected to another group of electro-acupuncture (Hwato SDZ-IIB type electro-acupuncture instrument, Suzhou, China). The researcher set the frequency at 2/15Hz, the intensity at 2mA, and the time at 30min, and alternately acupuncture/electro-acupuncture at bilateral auricular acupoints. All patients will be treated once a day, 6 sessions per week for 4 weeks.

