In this investigation, the antidepressants used for the control group are selective 5-hydroxytryptamine reuptake inhibitors (SSRIs), which have been shown to lower the risk of depression but may also raise the risk of fractures, seizures, brain hemorrhage, and gastrointestinal symptoms [9, 33]. The acupoints selected for the experimental group in this study are particular acupuncture points (Baihui(GV20), Yintang(EX-HN3), Fengfu(GV16), auricular concha, i.e., ear acupuncture acupoints Xin(CO15) and acupoints Shen(CO10)) in addition to the XNKQ acupuncture method of electro-acupuncture connection. Recent studies by Cai W et al [13] have indicated that electro-acupuncture (EA) appears to be an effective and safe therapy for PSD, with EA reducing depressive symptoms and improving neurological function. Several RCTs have proven the clinical efficacy of (electro)acupuncture in Baihui (GV20) and Yintang (EX-HN3) [34–38]. This is in close relation to the activation of the prefrontal lobes of the brain, which has been proven. In particular, Zhang, Z, J et al demonstrated that the use of an integrative acupuncture approach (electroacupuncture stimulation with body acupuncture) for the treatment of PSD, especially electrostimulation, reduced PSD and cognitive dysfunction [39, 40]. Fengfu (GV16) acupoint is located near the high cervical spine on the back and improves the blood supply of the vertebral artery. Several animal research and clinical data in recent years have demonstrated the effect of percutaneous vagal nerve stimulation on depression and even severe depression for the selection of auricular acupoints [3, 41, 42]. Among them, Wang, J. Y et al used the auricular concha region for stimulation and found an α7nAchR/NF-κB pathway associated with its antidepressant effect. These several pieces of high-quality evidence illustrate the importance of treatment of the auricular region for depression.

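### The article does not consistently say whether the experimental arm also takes escitalopram, so the contrast behind HAMD-17 and the serum markers is unclear

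*Protocol article*

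**What the plan says.** The two arms are described in several places.

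- **Abstract, Methods and analysis:** with usual stroke care as the background in both arms, "the control group will receive XingnaoKaiqiao (XNKQ) acupuncture, and the experimental group will receive antidepressant acupuncture at the same time as XNKQ acupuncture". No antidepressant drug is mentioned for either arm.
- **Section 2.1:** the first group has XNKQ acupuncture as its main treatment, and "escitalopram will be taken orally, and the other group will receive antidepressant acupuncture in addition to the above acupuncture treatment". Two lines later: "All acupuncture treatments will be given six times a week for four weeks (orally take escitalopram tablets daily for 4 weeks", with no arm named.
- **Section 2.5, opening paragraph:** care common to all patients is rehabilitation plus medication for stroke and its underlying conditions. No antidepressant is named there.
- **Section 2.5.1 (control):** XNKQ acupuncture, then "Oral escitalopram tablets 10mg Qd for 4 weeks".
- **Section 2.5.2 (experimental):** "The exact XNKQ acupuncture as in the control group is given", followed by the antidepressant acupuncture and electro-acupuncture. No drug is listed.
- **Section 3 Discussion:** one paragraph says that "the antidepressants used for the control group are selective 5-hydroxytryptamine reuptake inhibitors (SSRIs". The next cites meta-analyses favouring acupuncture combined with drugs.

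On the serum markers, the Introduction states: "As antidepressant drugs can cause changes in inflammatory factors".

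**The concern.** A two-arm trial estimates the effect of whatever differs between the arms. Here the descriptions support two different contrasts:

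- **Add-on:** both arms take escitalopram, and the arms differ only in antidepressant acupuncture.
- **Replacement:** only control takes escitalopram, so the arms differ in two components, one added and one withheld.

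These answer different clinical questions, and the same HAMD-17 result would carry a different conclusion under each. The mechanistic aim is more exposed still. The trial wants to read changes in IL-1β, IL-10, 5-HT and BDNF as an effect of acupuncture. If one arm alone takes an SSRI, a drug class that the Introduction itself links to inflammatory factors is unbalanced between the arms by design, and randomisation does not remove that.

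**Working it through.** **1. Setting the descriptions side by side**

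| Place | Drug in control | Drug in experimental | Points to |
|---|---|---|---|
| Abstract | not mentioned | not mentioned | arms differ only in antidepressant acupuncture |
| 2.1, description of groups | yes | not mentioned; only the acupuncture is carried over | control only |
| 2.1, parenthesis | no arm named | no arm named | both arms |
| 2.5.1 and 2.5.2 | yes | not listed; only XNKQ is carried over | control only |
| Discussion, SSRI paragraph | yes | not mentioned | control only |
| Discussion, combination paragraph | not specific | not specific | both arms |

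The shared care in section 2.5 names no antidepressant, so the drug cannot be taken as background on that basis. Nor can it come in as earlier treatment, since section 2.2.2 excludes patients treated with antidepressants within 2 weeks. The combination paragraph is a pointer and not proof, because it also cites reviews that set acupuncture against antidepressants.

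**2. What the HAMD-17 difference estimates**

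Let *a* be the effect of antidepressant acupuncture and *e* the effect of escitalopram on HAMD-17 reduction, both on an XNKQ background and, for simplicity, additive.

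- Drug in both arms: (*a* + *e*) − *e* = *a*.
- Drug in control only: *a* − *e*.

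Under the second reading a null result would mean *a* = *e*, not *a* = 0. The same algebra applies to each serum marker. The documents give no value for *e* on any outcome, so the gap between the two quantities cannot be put in numbers.

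**3. The plan's own sample size (section 2.5.3)**

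Inputs: two-sided α = 0.05, power 0.90, σ = 1.96, δ = 6.13 − 4.57 = 1.56, dropout 20%.

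- n = 2 × (1.960 + 1.282)² × 1.96² / 1.56² = 33.17 per group.
- Allowing for dropout: 33.17 / 0.8 = 41.47, rounded up to 42 per group, 84 in total. Rounding to 34 first gives 34 / 0.8 = 42.5, so 43.

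The stated 42 reproduces.

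**4. Where δ depends on the answer**

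Section 2.5.3 does not say whether the pilot arms took escitalopram. The 1.56 is therefore an estimate of *a* or of *a* − *e*, depending on the pilot regimen. If the pilot used the trial's contrast, whichever that is, 1.56 and the planned 90% power stand unchanged. If it did not, δ is an estimate of something else.

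**The case against.** The strongest reply is that the authors plainly meant an add-on trial, that an article condenses, and that Fig 1 or the full protocol may list each arm's treatments. Part of this stands. The figure is not available here, and the finding concerns the article's text, not necessarily how the trial is run. No two sentences state opposite things about the experimental arm, so this is inconsistent definition and not flat contradiction. But it is not detail left to a fuller document either. The sections that define the arms, followed as written, give the drug to control only, while other parts of the same article describe a contrast in acupuncture alone.

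A reader might infer more, and the documents do not support it:

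- **That a third trial is described, with no drug in either arm.** This rests only on the abstract's silence. Section 2.1, section 2.5.1 and the Discussion all say that the drug is used.
- **That only the acupuncture increment is randomised on every reading.** If the drug is in control only, escitalopram is randomised too.
- **That the trial is underpowered.** A loss of power needs an assumed drug effect and a pilot contrast that differs from the trial's. The documents supply neither.

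**Conclusion.** The concern holds as a problem of definition. Whether escitalopram is given in one arm or both is not consistently stated, and the answer decides whether the primary result is the added effect of antidepressant acupuncture or a comparison of it with escitalopram on an XNKQ background. Under the control-only reading, neither the HAMD-17 difference nor the serum differences could be attributed to acupuncture alone. For the cytokines this rests on the Introduction's own statement about antidepressant drugs. For HAMD-17 it needs only that the drug has some effect on depression.

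The size of the distortion cannot be derived from the documents. No error in the sample size is claimed. Because the choice of contrast governs every efficacy conclusion, it should be settled in writing before the results are analysed.

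**What to change.** Reconcile the abstract, sections 2.1, 2.5.1 and 2.5.2, and both Discussion paragraphs into one explicit list of co-interventions per arm, stating for each arm whether escitalopram is given. The list should match the version that the ethics committee approved. Which regimen is right is for the investigators.

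Then:

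1. State the contrast that results: either antidepressant acupuncture as an add-on to a shared background, or antidepressant acupuncture versus escitalopram with XNKQ in both arms.
2. Word the objective and the conclusions, including those on the serum markers, to match that contrast.
3. Confirm in section 2.5.3 that the pilot difference of 1.56 came from the same contrast.

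The cost is wording plus a clarification to the ethics committee and the registry. If the pilot proves to have tested a different contrast, the basis for δ has to be revisited, and whether that changes the sample size cannot be said from these documents.

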**Fig 1 pone.0303162.g001:**
[figure not shown]
The flow chart of this trial.

**Table 1 pone.0303162.t001:** The chart of enrollment and assessment.

Timepoint	Study period			
	Enrollment	Baseline	Treatment Phase Week 2	Treatment Phase Week 4
**Enrollment**				
Informed consent	**×**			
Demographic information	**×**			
Basic vital signs	**×**			
Medical history	**×**			
Merger disease	**×**			
Eligibility screen	**×**			
Randomization		**×**		
**Interventions**				
Experimental group		**×**	**×**	**×**
Control group		**×**	**×**	**×**
**Assessments**				
HAMD-17		**×**	**×**	**×**
SDS		**×**	**×**	**×**
NIHSS		**×**	**×**	**×**
MBI		**×**	**×**	**×**
Serum laboratory index		**×**		**×**
Serum metabolomics		**×**		**×**
**Safety**				
Safety evaluation		**×**	**×**	**×**
Adverse events		**×**	**×**	**×**
Merger medication		**×**	**×**	**×**

#### 2.1.1 Ethical approval and study registration

This study protocol was approved by the Medical Ethics Committee of the First Teaching Hospital of Tianjin University of Traditional Chinese Medicine (item number: TYLL2023[Z]004) and was registered with the China Clinical Trial Registry (item number: ChiCTR2300071386)

#### 2.1.2 Informed consent

The study will be carried out following the Declaration of Helsinki formulated by the World Medical Association and relevant clinical research regulations in China. Before patients are enrolled in this study, the researcher is responsible for fully and comprehensively introducing the purpose, procedure, and possible risks of this study to him or his designated representative in written form. Patients should be made aware of their right to withdraw at any time. All participants will obtain written informed consent before enrollment. The researcher will ensure that each patient signs an informed consent form before participating in the study, which will be kept in the study file. Patients who may be pregnant must be informed that if they get pregnant during the study, the study may endanger the fetus. Before taking part in this study, the patient should agree to use contraception during the study.

